### Blinding

We have built in 4 strategies to ensure blinding: randomization using permuted blocks, all investigators blinded to group assignments (except the biostatistician [name]), all participants blinded to the study aims and reminded as needed not to discuss their experiences with the outcome assessor, and outcome assessors blinded to the study aims, group assignments, and previous test results, and to interact with participants only for data collection [67]. Assessors will not interact with other staff who are not blinded and will participate in separate meetings. Blinding success will be assessed after each data collection: Was group assignment unveiled? Why? For participants whose group assignments are revealed, a different blinded assessor will collect subsequent data. Other strategies include the use of standardized intervention protocol, forms, and reliable and valid variable measures. The analyses will incorporate all design features (e.g., repeated measures within persons, missing data). Unblinding to investigators and study team will only occur when the data analysis of the primary outcomes is completed.

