### Data analysis

#### Determine the intervention effect on outcomes

All primary analyses will follow *the intention-to-treat principle* (e.g., group assignment in the analysis will be based on randomized group assignment regardless of the level of adherence to provide unbiased comparisons of the effects among the groups). This principle will account for any potential data loss. We will fit linear mixed-effect models for each outcome measure, accounting for repeated measures at baseline, post-intervention, and 6- and 12-month follow-up. The models will include fixed effects for data collection visit (categorical variable), group assignment (compare the combined group with other groups), visit and group interaction, respective baseline outcome measure, and covariates identified as being imbalanced among groups. Stepwise variable selection using Akaike Information Criteria will be used to select the fixed effects for inclusion. A random participant-specific effect will be included to account for correlation between visits in the same participant. The model-based average within-group change in outcome measure for each group will be computed at each post-intervention and follow-up point. This will allow us to rank the groups in terms of average within-person gains in each outcome measure. In addition, *the effect sizes of RFB+VSOP and IR+VSOP control for each outcome measure* will also be calculated using standardized mean difference with 95% CI [(*M*_int_ − *M*_control_ at later time) − (*M*_int_ − *M*
_control_ at baseline)]/intra-participant standard deviation; “int” refers to combined intervention or VSOP; “control” here refers to attention control. The effect size of RFB+VSOP will be compared with that of the IR+VSOP control group to determine the additive effect.

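### Stepwise AIC is applied to the primary model's fixed effects with no term protected, so as written the data decide whether group and visit-by-group stay in

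*Protocol article*

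**What the plan says.** The rule is in the Protocol article, Data analysis, under Determine the intervention effect on outcomes. The subsection opens with the primary, intention-to-treat analyses ("All primary analyses will follow" that principle). It specifies a linear mixed model for each outcome, "accounting for repeated measures at baseline, post-intervention, and 6- and 12-month follow-up".

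- **Fixed effects:** categorical visit, then "group assignment (compare the combined group with other groups), visit and group interaction, respective baseline outcome measure", and finally "covariates identified as being imbalanced among groups".
- **Selection rule, in the next sentence:** "Stepwise variable selection using Akaike Information Criteria will be used to select the fixed effects for inclusion".
- **Random part:** "A random participant-specific effect will be included to account for correlation between visits in the same participant".
- **Use of the model:** average change within each group is to be computed at the post-intervention visit and at each follow-up, and the groups are then ranked on these gains.

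**The concern.** The selection sentence uses the same term, fixed effects, that has just been used for the whole list. It neither protects the design terms nor limits selection to covariates. Taken at its word, AIC may delete visit-by-group, which carries the visit-specific treatment effect, and then group itself.

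Three things are at stake:
- **The planned output may not exist.** Without visit-by-group, the four-visit model gives every group the same change from baseline and there is nothing to rank. Without group as well, there is no treatment contrast.
- **Estimates and intervals after selection are unreliable.** A treatment term tends to survive when chance has made the effect look large, and ordinary intervals ignore this.
- **Outcomes may not be comparable.** Models are fitted outcome by outcome, so the treatment contrast can be a different quantity for each.

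The rule is stated outright in the article. It is not a detail left to an SAP: an SAP that forced the treatment terms in would have to contradict this sentence.

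**Working it through.** **1. The sentences side by side.** The list contains group and visit-by-group. The selection sentence acts on the fixed effects without exception. The sentences after it need change by group and visit, which the model can supply only if both terms are present. The section therefore conflicts with itself unless selection is confined to covariates, and it does not say that.

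**2. Inputs.**
- From the article: three groups, 38 per group (114 in all), four visits, a participant random intercept, d = 0.20 and alpha 0.025 per comparison (Sample size).
- Assumed: two-sided testing (sidedness is not stated); within-person correlation 0.7, with 0.5 to 0.8 as the range (the article gives none); no dropout; and a treatment effect that is constant from post-intervention onward.
- The article gives no figure on selection to reproduce. Its N = 96 comes without power or correlation, and this point does not rest on it.

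**3. The AIC rule.** A term with k degrees of freedom is kept if the likelihood-ratio statistic exceeds 2k. For a truly null term the chance of retention is P(χ²ₖ > 2k):
- group, k = 2: e⁻² = 13.5%
- visit-by-group with three post-baseline visits, k = (3−1)(3−1) = 4: e⁻⁴(1 + 4) = 9.2%
- visit-by-group with four visits, k = (3−1)(4−1) = 6: e⁻⁶(1 + 6 + 18) = 6.2%

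In a balanced random-intercept model with N = 114 and m visits as responses, visit-by-group is kept if N(m−1)·ln(RSS_within,0 / RSS_within,1) > 2k. Group is kept if N·ln(RSS_between,0 / RSS_between,1) > 4.

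**4. Simulation at the design effect (d = 0.20, 38 per arm, correlation 0.7).** The text allows two layouts, so both were run.

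| | Baseline is response and covariate (4 visits) | Baseline is covariate only (3 visits) |
|---|---|---|
| All group terms dropped | 43% to 44% | about 41% |
| Mean 12-month estimate, visit-by-group kept | 0.30 to 0.31 | 0.19 |
| Mean estimate, only group kept | not used here (see objection) | 0.27 to 0.28 |

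In the four-visit layout visit-by-group is dropped in 79% of trials. Without selection the mean estimate is 0.20. In the three-visit layout a constant effect leaves no true interaction, so inflation comes through the group term.

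**5. Sensitivity (three-visit layout, effect averaged over visits).**
- 32 per arm, d = 0.20: some group term is kept in 47.0% (correlation 0.5) to 63.6% (0.8), so all are dropped in 53.0% to 36.4%. The mean when kept is 0.289 to 0.252, that is 0.289/0.20 = 1.45 and 0.252/0.20 = 1.26 times the truth.
- Counting a dropped term as zero, the mean is 0.14 to 0.16 and coverage of the 97.5% interval is 0.46 to 0.62. With the terms forced in, the mean is 0.20 and coverage 0.975 to 0.979.
- 38 per arm, correlation 0.5: kept in 50%, mean when kept 0.28.
- d = 0.50, 32 per arm: kept in 97% to 100%, mean when kept 0.50 to 0.51. The distortion nearly vanishes.

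**6. No true effect.** Among trials that keep a group term (32 per arm), 11.6% or 10.8% reject at 0.025 and coverage is 0.88 to 0.89. A trial that drops the terms does not reject, so the unconditional rates are 0.233 × 0.116 = 0.027 and 0.230 × 0.108 = 0.025. With 38 per arm and correlation 0.7 the unconditional rate is about 0.033 to 0.034.

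**The case against.** **The milder reading.** The list is introduced as what the models will include, and only its last item, the imbalanced covariates, depends on the data. The group-by-visit changes also presuppose that the treatment terms stay. On that view AIC screens covariates only. This is coherent and may be what was meant, but the article does not say it, and making it true needs the same short edit. Even then, covariates would be chosen by observed imbalance and again by AIC, separately for each outcome.

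**A contrast outside the model.** The section also defines a standardised difference in differences with a 95% CI, written in group means. If raw means are used, selection cannot touch it. That stands, but the article does not say whether the means are raw or modelled, and this measure is additional to the mixed model.

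**Stronger inferences that the documents do not support.**
- *A badly inflated type I error.* One could cite the roughly 17% of null trials with p < 0.025 among those keeping a group term in the four-visit layout. That figure is conditional on survival and mixed with a standard-error problem from baseline's double role. In that layout the unconditional rate is about 0.034 with AIC against 0.056 with the terms forced in, so AIC is not the source of the excess. With post-baseline visits only it is 0.033 against 0.024.
- *Dilution of the effect by AIC.* At d = 0.40 in the four-visit layout, the group-only estimate averages 0.24. This arises because baseline, where the effect is zero, is among the responses. With post-baseline visits only, the group-only estimate is 0.41.
- *Steering by the unblinded biostatistician.* The Blinding section does exempt the biostatistician, but stepwise AIC is an algorithm and the documents show no route by which knowledge of allocation would direct it.

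**Conclusion.** The point holds as a defect in how the primary model is fixed. The selection rule covers the treatment terms by its wording and conflicts with the planned use of the model. That the treatment terms will be put at risk is the literal reading, not a certainty.

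On that reading, at the effect the trial is sized for, about 41% to 44% of trials would lose every group term. Surviving estimates would typically be about 0.28 to 0.31 against 0.20. This depends on layout and route: in the three-visit layout with visit-by-group kept, there is no inflation. Intervals would take no account of selection, and the contrast could differ between outcomes. Type I error is not the main harm. The sizes rest on the assumed correlation, no dropout and a sustained effect, and they shrink to almost nothing at d = 0.50.

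**What to change.** Delete the stepwise sentence from the primary analysis. State instead that visit, group, visit-by-group, the baseline value and the age stratum used in randomisation are retained for every outcome, and that the pairwise contrasts are read from that model. Confine AIC to exploratory or sensitivity models, such as a check on additional covariates.

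At the same time, settle whether baseline is a response or a covariate. Removing the stepwise rule alone leaves that separate problem in place (rejection of 0.056 under the null in the four-visit layout with terms forced in).

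The selection change costs about one sentence and needs no extra data or resources.

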#### Determine the relationships between changes of outcomes

We will first examine correlations between the changes of central and peripheral measures of ANS at rest and reactivity, respectively, from baseline to later time points for the entire sample. Next, we will use the mixed-effect model to determine the main and interaction effects of change in ANS measures (primarily, reactivity) and group on changes of each dementia progress measure (comparing baseline to later time points). Performing this analysis is to determine whether a change in ANS flexibility will lead to greater improvement in dementia progress measures in the combined intervention group, compared to other groups.

## Discussion

We capitalize on adding RFB practice to VSOP to modify ANS flexibility, which we in turn hypothesize will further strengthen the effect of VSOP on multiple markers of dementia progress. Adaptation capacity to environmental demands contributes to long-term cognitive and functional maintenance in old age regardless of the effect of neurodegeneration. Therefore, enhancing ANS flexibility, essential for adaptation capacity, may impact the long-term cognitive and functional outcomes in old age, including those at risk for dementia. RFB provides a bottom-up modulation that may directly enhance the neurobiological adaptation during VSOP training that is required for neuroplasticity. Further, along with enhanced neuroplasticity and cognitive outcomes, we suggest that combining RFB and VSOP will strengthen overall adaptation capacity better than VSOP alone. Together, these effects are hypothesized to slow dementia progress. Such a combined intervention approach is novel, but grounded in a solid mechanistic understanding.

Our work is inspired by a novel conceptual framework of “physiological geroscience,” which proposes a primary-prevention approach to addressing aging-associated physiological factors that in turn can slow aging and extend the healthspan [68]. Seals et al. suggest that optimizing physiological function via lifestyle interventions, pharmaceuticals, etc., in the aging process can slow down the decline of other interrelated functions (e.g., cognitive function and neurodegeneration) and delay the incidence of aging-associated diseases (e.g., dementia). We are among the first to apply this approach to examine whether modifying ANS flexibility, and therefore increasing adaptation capacity, can slow the progress of dementia. The components of ANS flexibility are vulnerable to aging. Vascular-wise, aging-related decline in endothelial function leads to changes in baroreflexes [69]; neurologically, aging-related decline is implicated in the decreased neural efficiency of central autonomic networks [70]. Both mechanisms can cause the disruption of the ANS flexibility [10, 71], which in turn affects the regulation of self-oriented behaviors, including stress adaptation.

Furthermore, the therapeutic implication may be different between studying primary- (e.g., adaptation capacity) vs. secondary- (e.g., hippocampal atrophy) prevention factors for the progress of dementia. This is crucial for aging populations since they are often exposed to heterogeneous health conditions that impose secondary adverse effects on the progress of dementia. Enhancing common preventative factors may strengthen cognitive and brain function across different conditions in which secondary-prevention factors can be too heterogenous to be modified via a common pathway.

Adaptive cognitive training programs hold great promise for slowing progression to dementia in older adults with MCI. The research proposed here translates the growing understanding of the top-down and bottom-up regulation of integrated central and peripheral systems to bolstering the transferred and long-term effects of cognitive training and reducing the burden of dementia for patients, caregivers, and the health care system. Additionally, findings from the proposed study may have implications in addressing the long-lasting public health concerns on the impact of maladaptation to stress on neurodegeneration [72]. After completion of the clinical trial, relevant results will be presented in community settings and published in peer-review research journals. Further stages of clinical trials (e.g., stage 3) will be proposed, or modified if needed, to test the effectiveness of the intervention.

## Data Availability

We will create a database for hosting all data at the University of Rochester (UR) and managed and stored by the UR Information Analyst on-site. A final complete database will be created to host all data which will be stripped of any identifiers and stored pursuant to UR Institutional Review Board protocols. After data entry, cleaning, and linkage, the Information Analyst will provide the research team a de-identified data set for purposes of analysis and manuscript preparation. We will make the data and associated documentation available to users only under a data-sharing agreement as suggested by the NIH that provides for (1) a commitment to using the data only for research purposes and not to identify any individual participant, (2) a commitment to securing the data using appropriate computer technology, and (3) a commitment to destroying or returning the data after analyses are completed. The richness of the data, combined with the interdisciplinary nature of the research team, provides opportunities for future wide disseminations. The interdisciplinary team has a strong history of presenting at local, state, and national conferences that span the fields of neuroscience, gerontology, cognition, and psychophysiology. It is of the utmost importance to this team that the work products from this study will be disseminated in a manner that provides implementation in the field.
